#### Evaluation forms for the clinician

##### Clinician baseline form

This form serves for the registration of the patient at the baseline evaluation and focuses on the collection of patient profile specifics and their hearing history. It also collects information related to the implanted device/s and the external sound processors to be used, as well as any clinical details such as patient comorbidities, surgical approach, aetiology of the disease and hearing history. Questions in relation to number of weeks of gestation, physical balance, dizziness, commonly used mode of communication, physical and mental impairment, and other comorbidities and syndromes were included. Additionally, the questionnaire comprises questions on sources of referral and funds for implantation.

##### Clinician follow-up form

This form corresponds to the Clinician Baseline Form and is to be completed at each subsequent follow-up. The questions are designed to capture any changes that may have occurred since the previous evaluation interval, including details of any new implanted device/s and external sound processors. Additionally, it collects information regarding compliance to device use and therapy, the quality of family’s participation in the child’s habilitation and the clinician’s satisfaction with the patient’s progress [40].

##### The Categories of Auditory Performance – II (CAP-II)

The CAP is a widely-used, simple, language-independent, and culturally adaptable measure of auditory performance suitable for assessment in children of all ages, including patients less than age four years [37]. The majority of the literature, to date, has used the eight-point hierarchy rating scale of the CAP that assesses a child’s functioning in everyday situations. It covers a range of auditory performance abilities and also takes into consideration the different developmental rates of children. The CAP consists of a nonlinear, hierarchical scale with a score 0 equating to the lowest skill of, “no awareness of environmental sounds”, and a score 7 corresponding to the highest skill of, “use of telephone with a known listener”. Evidence shows a ceiling effect of the CAP as it does not address the more complicated listening skills now achievable with cochlear implants and other hearing devices, particularly when used in bilateral configurations. As such, an extension of the CAP was introduced in 2010, called the CAP-II [41].

The CAP-II, when compared to the CAP, adds two additional higher-level auditory skill categories to the original scale. As such, the CAP-II is a more sensitive measure of the range of auditory skills in hearing impaired children. Hence, the CAP-II was selected for use in the Cochlear P-IROS, to assess the patient-related auditory benefits arising from the use of implantable hearing devices in the unilateral and bilateral configuration compared with the pre-operative listening condition [14,20].

##### Unaided hearing thresholds form

This evaluation form collects unaided hearing thresholds measured through behavioural audiometry in the sound-field or via headphones for air-conduction and bone-conduction hearing thresholds performed routinely in the clinic. Thresholds for the speech frequency range 250 Hz 500 Hz, 1000 Hz, 2000 Hz, 4000 Hz and 8000 Hz are desired for measure and record for each ear. This form is used at the baseline visit following registration of the patient online, to capture the pre-implanted hearing thresholds for the patient. Subsequently post-operative hearing thresholds routinely measured for bone and air conduction in each ear may be recorded at follow-up intervals, using this form, as desired. For infants, where pure tone audiometry is not applicable, Otoacoutsic Emissions (OAE) and Auditory Brainstem Responses (ABR) may be recorded. Repeated hearing threshold measures may be compared over time to assess their stability following treatment.

##### Aided hearing thresholds form

This evaluation form collects aided hearing threshold levels for warble tones for each ear as routinely measured at the clinic through behavioural audiometry in the sound field, pre-operatively using a hearing aid and post-operatively using an implantable hearing device. Record of sound-field, aided hearing thresholds for warble tones in individual ears, where feasible, for the frequencies 250 Hz, 500 Hz, 1000 Hz, 2000 Hz, 4000 Hz and 8000 Hz, is desired at baseline and at follow-up intervals, six monthly intervals up to two years and annually up to five years post surgery. Repeated aided thresholds are compared over time and to unaided thresholds at the same time interval for determination of objective functional threshold gains.

##### End of study form

This form is completed for each registered patient upon his or her departure from the registry. This may be either at the completion of the prescribed set of evaluations (e.g., two, three, four, or five years post-implant) or prematurely at the request of the clinician or parent/caregiver or following an event requiring removal of the patient from further review. The clinician is asked to record the reason for premature termination of the review and subsequent data collection and date of exit from the study for each patient enrolled in the study.

#### Evaluation forms for the parent/caregiver

##### Implant recipient baseline/follow-up forms

These forms are self-administered by the parent/caregiver at baseline and follow-up intervals to collect complementary patient-specific data to that gathered in the Clinician Baseline/Follow-up forms. They are designed to gather basic hearing experience information and patient characteristics, including hearing aid use prior to and after the surgery, age at implantation, familial socio-economic factors, educational placement and communication mode, that may influence clinical and humanistic outcomes.

##### Children using Hearing Implants Quality of Life (CuHI-QoL)

This is a new Quality of Life instrument designed for this study, developed to assess quality of life of patients using implantable hearing devices via parent proxy (A copy of this questionnaire is available electronically) (Additional file 1). Its aim is to assess the impact of implantable hearing devices on the quality of life of very young patients, their parents’ expectations and the wellbeing of the family over time. A review of published literature on available health-related, quality of life instruments, hearing-health assessments and questionnaires used in the paediatric population and administered via parent proxy was undertaken during the development of this new measure. Specifically, an evaluation of the most commonly assessed domains and evidence of the corresponding sensitivity of the existing measures for implant treatment effects was reviewed. Published researchers of subjective scales used in the hearing-implant field were consulted to help determine the most relevant domains, content, and construct for this tool [42-48]. The resulting 25-item parent-reported questionnaire is divided into three sections; 1) Parental Expectations, 2) Impact on the Family, and 3) Quality of Life of the Child. The 25 questions cover the following domains; self–reliance, wellbeing and happiness, social functioning, general functioning, parental stress, and family cohesion. The questionnaire has been piloted to assess the feasibility and practicality of its use in multiple cultural (i.e., English and Asian) and socio-economic settings by parents and providers before being introduced as a tool for use in the study. The CuHI-QoL instrument is currently being validated by researchers at the Department of Audiology and Speech Therapy, University of Melbourne, Australia. The validation study includes parents of children with a hearing impairment who use either hearing aids or cochlear implants, and normal-hearing peers.

##### The Health Utilities Index - Mark III (HUI3)

The HUI3 is a generic health status and health-related quality of life questionnaire that was shown to be a sensitive measure to demonstrate impact of medical treatments over time across eight domains: vision, hearing, speech, ambulation, dexterity, emotion, dexterity, cognition and pain [48]. A number of studies demonstrate its effectiveness to determine the utility gained from implantable hearing devices [49-51]. The HUI3 version used in this study is suitable in children as young as age six years [48]. A conservative approach was taken for the Cochlear P-IROS, making the questionnaire available for patients greater than or equal to age 10 years at the time of enrolment. Validated translations have been licensed and made available specifically for use in this study.

##### The Speech, Spatial and Qualities of Hearing Scale (SSQ)

The SSQ scale is a standardised questionnaire that was shown to be a sensitive measure to demonstrate benefits of bilateral versus unilateral hearing ability in a variety of daily situations and a range of hearing abilities, across three domains: speech, spatial and quality in adolescents and adults [36]. Compared with the CAP-II, it provides more finely detailed information about a patients’ auditory performance in everyday situations, allowing for detailed analysis. This version of the SSQ is available for completion by enrolled patients greater than or equal to age 10 years at the time of implantation.

##### The SSQ-Parents’ version (SSQ-P)

The SSQ-P is available for response via parent proxy for enrolled patients aged four to 10 years at the time of implantation. Based on the original SSQ above, covering the same three domains, it was modified and shortened for administration as a self-assessment tool for parental proxy following observation of their child’s behaviour in various listening environments in their daily lives, as considered applicable [38]. The SSQ-P is not recommended for parental proxy of children less than age four years, as the developmental changes observed in these patients may confound the judgment and, subsequently, the measurement of intervention effect over time. The reasons include difficulties associated with accurately rating the performance of younger patients in questions such as, “following a group conversation” [38]. In the design of this questionnaire for use in non-English speaking countries, a validated translation process was employed (e.g., from English to Hindi and Hindi to English). Necessary cultural adaptations were also made as required (e.g., use of the term ‘motor scooter’ instead of a ‘lawn mower’ in India) through personal communications with [name] (University of New England, NSW, Australia), the co-developer of the original SSQ.

### Study hypotheses

#### Primary hypothesis

a. Post-implant performance for all patients on the Categories of Auditory Performance-II (CAP-II) are superior to pre-implant performance (baseline) and show incremental improvement at each subsequent post-implant assessment point (six months, 12 months, 18 months, 24 months, and annually for up to five years) during the study.

#### Secondary hypotheses

a. Post-implant hearing ability for patients > 4 years of age as assessed via the standardised Speech Spatial and Qualities scale Parents’ version (SSQ-P) are superior to their pre-implant hearing ability (baseline) and show incremental improvement at each subsequent post-implant assessment point (six months, 12 months, 18 months, 24 months, and annually thereafter for up to five years) during the study.

b. Post-implant auditory performance for patients using binaural hearing/stimulation is superior to that of patients using unilateral hearing/stimulation at each post-implant evaluation point (six months, 12 months, 18 months, 24 months, and annually thereafter for up to five years) during the study as measured by assessments of the:

i. Categories of Auditory Performance – II (CAP –II) scale for all patients

ii. Speech Spatial and Hearing Qualities Parents’ version (SSQ-P) scale

iii. Post-implant, aided hearing-threshold levels

#### Tertiary hypotheses

a. Post-implant assessment of quality of life for the patient and family via the CuHI-QoL questionnaire as assessed by the parent or caregiver are superior to quality of life assessed at baseline (pre-implant) and show incremental improvement at each subsequent post implant evaluation time point (six months, 12 months, 18 months, 24 months, and annually thereafter for up to five years) during the study.

b. Patients who begin mainstream school during the study enter at an age-appropriate time.

c. The proportion of patients who are participating in mainstream school with no additional support is higher than the proportion of patients in other categories of school placement.

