As a step towards generating a consistently collated and reported dataset on children implanted with hearing devices, the Cochlear Paediatric Implanted Recipient Observational Study (Cochlear P-IROS) was developed. This global, prospective, observational study provides for, and facilitates, a more unified approach for the assessment of patient outcomes cross-culturally, in a structured, sustainable and easily accessible format. The Cochlear P-IROS study design is based on the primary hypotheses of intra-subject improvements in auditory performance of children using implantable hearing devices across diverse language and cultural settings. A consistent set of questionnaire-based assessments and patient-related information will be collected via a web-based electronic data capture (EDC) platform.

The purpose of this paper is to introduce the design and methodology of the Cochlear P-IROS registry. The objectives of the study are threefold:

a) To evaluate the longitudinal improvements in auditory performance with implantable hearing devices in children using standardised questionnaires.

b) To provide statistically significant data to support patient management decisions at the clinical, regulatory, payer and policy level.

c) To compare the patient-related or humanistic benefits such as educational attainment, quality of life and patient satisfaction resulting from use of hearing implants in unilateral, bilateral and bimodal configurations.

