#### Population

The Cochlear P-IROS will enrol infants and children up to age 10 years, at the time of intervention. Children (referred to as ‘patients’), may receive any brand of regulatory approved implantable hearing device including any type of cochlear, bone conduction, electroacoustic or other implantable hearing device. If required, the Cochlear P-IROS platform also permits the capture of data from patients implanted at age 10 years or above, to address the growing trend for intervention in older children with an acquired or progressive hearing loss [30]. Additional questionnaires appropriate for this age bracket have been included for completion by these individuals' proxies. Patients above age 10 years may also be entered into the Cochlear IROS platform, a corresponding registry platform already implemented for adult patients.

The specific inclusion and exclusion criteria of the study are as follows:

Inclusion criteria:

1. Newly implanted prelingual and perilingual patients less than age 10 years, prior to the first time the hearing implant system is activated by the fitting of the sound processor.

2. Unilateral, bilateral or bimodal users of cochlear implants, electroacoustic devices, bone conduction implants, or other implantable hearing systems.

3. Parent/caregiver and/or patient are cognitively able to respond to self-administered/proxy assessment scales and willing to participate and sign the Patient Informed Consent form.

Exclusion criteria:

1. Patients with previous hearing implant experience. This includes all brands and types of cochlear, bone conduction, electroacoustic and auditory brainstem implant systems.

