#### Study period

The Cochlear P-IROS registry will be available for clinics on a voluntary basis for monitoring the long-term progress of patients and sub-groups of patients using hearing devices. The recruitment of study sites is ongoing. Any implant clinic may join the Cochlear P-IROS to gather longitudinal data for newly implanted and enrolled patients at their discretion. For patients enrolled, baseline registration is scheduled post-implant, which may ideally be at any time after surgery and prior to the first time the hearing implant system is switched on by the fitting of the externally worn sound processor. Typically, activation occurs at two to four weeks post-operation. As illustrated in Table 1, suggested follow-up evaluations may be recorded at six months, 12 months, 18 months, 24 months, and annually thereafter for up to five years, ideally in parallel to routine clinical visits. Once a clinic voluntarily enrols a patient, it is assumed that adherence to the study protocol will occur, including a submission of their respective follow-up data for a minimum of two years post-surgery. Further evaluation of the patient, in the longer term, will remain optional. As the registry is entirely investigator-driven, the clinician is responsible for counselling and ensuring that the patient and their family are sufficiently motivated to participate in the study, long-term, while maintaining the decision for their participation as voluntary.

**Table 1 T1:** Cochlear P-IROS evaluation schedule illustrating electronic case report forms used against the recommended evaluation time-point

**Electronic case report form**	**Evaluation time point (Months post-implant)**							
	**0**	**6**	**12**	**18**	**24**	**36**	**48**	**60**
Clinician baseline form	■	**-**	**-**	**-**	**-**	**-**	**-**	**-**
Clinician follow-up form	**-**	■	■	■	■	□	□	□
Implant recipient baseline form	■	**-**	**-**	**-**	**-**	**-**	**-**	**-**
Implant recipient follow-up form	**-**	■	■	■	■	□	□	□
Children using Hearing Implants Quality of Life (CuHI-QoL) Questionnaire	■	■	■	■	■	□	□	□
Health Utility Index Mark III (HUI3)**	■	■	■	■	■	□	□	□
Categories of Auditory Performance-II (CAP-II) Questionnaire	■	■	■	■	■	□	□	□
Speech Spatial Qualities (SSQ) Parents Version Questionnaire (SSQ-P)	□	□	□	-	□	□	□	□
Speech Spatial Qualities (SSQ) Standard Version**	□	□	□	-	□	□	□	□
Unaided hearing thresholds form	□	□	□	□	□	□	□	□
Aided hearing thresholds form	□	□	□	□	□	□	□	□

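### Tertiary hypothesis b counts only children who enter mainstream school during follow-up, which pushes the on-time share upward; hypothesis c has no reference, and neither makes the comparison promised in objective c

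*Protocol article*

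**What the plan says.** Under Tertiary hypotheses, b states: "Patients who begin mainstream school during the study enter at an age-appropriate time". Hypothesis c states that the share in mainstream school without extra support "is higher than the proportion of patients in other categories of school placement".

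The third objective, in the Background, is "To compare the patient-related or humanistic benefits such as educational attainment, quality of life and patient satisfaction" across unilateral, bilateral and bimodal use.

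On follow-up, the Study period section expects adherence "including a submission of their respective follow-up data for a minimum of two years post-surgery", and adds: "Further evaluation of the patient, in the longer term, will remain optional". Table 1 agrees: the recipient follow-up form is required at 6 to 24 months and optional at 36, 48 and 60 months.

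The first inclusion criterion is "Newly implanted prelingual and perilingual patients less than age 10 years, prior to the first time the hearing implant system is activated", so both infants and children already of school age can be enrolled. The section on the parent/caregiver forms says that they collect, among other items, "familial socio-economic factors, educational placement and communication mode, that may influence clinical and humanistic outcomes". Table 3 likewise lists educational placement; no listed tool measures attainment.

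**The concern.** Hypothesis b selects on a post-implant event. A child in a special school, at home, or not yet in mainstream school at exit is not a failure under b; that child is absent from it. An analysis plan that follows the sentence faithfully inherits the selection, so this is not a detail merely left to that plan.

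Hypothesis c does not say whether the other categories are taken one by one or together, and it sets the placement mix against nothing outside itself: no baseline, no external population, no other device group.

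The article presents educational placement as a gap in existing evidence that matters to payers and policy makers. A high on-time percentage, or a statement that unsupported mainstream is the leading category, could be quoted to them as educational benefit although neither result bears on it.

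**Working it through.** **Inputs.** From the Protocol article: two years of required follow-up, optional to five; age under 10 at implantation; the wording of b and c. The article gives no school-entry age, number of placement categories or expected proportions, so those below are assumptions. Its only sample size, n = 50, is for CAP-II, so there is no stated figure for the school hypotheses to reproduce.

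**Hypothesis b, simple count.** Suppose that of 100 children reaching school age 50 enter mainstream on time, 20 enter late and 30 do not enter.
- All children reaching school age: 50/100 = 50%.
- As worded, all late entrants seen: 50/70 = 71%.
- As worded, half the late entrants start after exit: 50/60 = 83%.

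**Hypothesis b, with follow-up truncation.** Let p_on, p_late and p_never sum to 1, and let s_on and s_late be the probabilities that an entry falls inside follow-up. Then

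share under b = p_on·s_on / (p_on·s_on + p_late·s_late).

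Assume entry is due at 6, late entry comes 1, 2 or 3 years later with equal probability, and implant age is uniform over 3 to 6 years. With F years of follow-up, entry at age e is seen if implant age lies between e − F and e.
- F = 2: s_on = 2/3; s_late = (1/3)(1/3 + 0 + 0) = 1/9.
- F = 5: s_on = 1; s_late = (1/3)(1 + 1 + 2/3) = 8/9.

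| True on-time / never / late | b, 2 years | b, 5 years |
|---|---|---|
| 70 / 10 / 20% | 0.467/(0.467 + 0.022) = 95% | 0.70/(0.70 + 0.178) = 80% |
| 50 / 20 / 30% | 0.333/(0.333 + 0.033) = 91% | 0.50/(0.50 + 0.267) = 65% |
| 10 / 30 / 60% | 0.067/(0.067 + 0.067) = 50% | 0.10/(0.10 + 0.533) = 16% |

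**Sensitivity to implant age.**
- 0.5 to 5 years, F = 2: a late entry at 7 or older cannot be seen, so b reads 100% whatever the truth.
- 0.5 to 5 years, F = 5, true 50%: s_on = 4/4.5 and s_late = (1/3)(3 + 2 + 1)/4.5 = 2/4.5, giving 2.0/(2.0 + 0.6) = 77%.
- 0.5 to 10 years: s_on = s_late = F/9.5, so truncation cancels and only the omission of children who never enter remains. A true 50% reads as 0.5/0.8 = 63%, and a true 10% as 0.1/0.7 = 14%.

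**Hypothesis c.** Read category by category with k categories, any share just above 1/k can be the largest: 33%, 25% and 20% for k = 3, 4 and 5. With five categories, 30% + 4 × 17.5% = 100%, so c would hold with 70% of children placed elsewhere. Read as all others combined, c needs more than 50%.

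Simulated probabilities with four assumed categories, unsupported mainstream listed first:

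| True shares (%) | Observed largest, n = 50 / 200 / 1000 |
|---|---|
| 40/30/20/10 | 0.77 / 0.95 / 1.00 |
| 35/35/20/10 | 0.45 / 0.49 / 0.50 |
| 30/40/20/10 | 0.17 / 0.04 / 0.00 |

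On the combined reading, a true 40% share succeeds with probability 0.06 at n = 50 and about 0 from n = 200. The two readings therefore give opposite answers for the same children.

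**Objective c against the hypotheses.** The objective promises a comparison of configurations. Hypotheses b and c each describe one pooled group. The only configuration contrast among the hypotheses, secondary b, concerns auditory performance.

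**The case against.** A reader might infer that both school hypotheses are built so that success is nearly assured. The documents do not support that. Hypothesis b fixes no success threshold, and a late entrant seen during follow-up counts against it. Enrolment runs to age 10, and children implanted after school-entry age can appear under b only as late entrants. They pull the share down, and in a cohort made up mostly of such children b could even understate timely entry. Near-certainty arises only in a special case: young implantation with two-year follow-up. Two years is also a minimum, and visits to 60 months are offered. Hypothesis c fails whenever another category is larger, and taking it as a plurality is only one reading of the sentence.

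It can also be said that c covers children in other placements, so the pair is less blind than b alone; that placement categories, a school-age restriction and the exact comparison may be settled in the separate analysis report; and that these are tertiary hypotheses in an observational registry.

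Most of this stands, and it limits the claim. It does not remove the selection in b, which is written into the hypothesis, or the mismatch with objective c. The single-or-combined question in c is largely a clarification.

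**Conclusion.** The point holds in a limited form. Hypothesis b leaves out children who never enter mainstream school and those who enter after exit. For children followed from before school-entry age this inflates the on-time share. In the cases worked with a true 50%, b reads from about 63% (implantation at 0.5 to 10 years) through 91% (3 to 6 years, two-year follow-up) to 100% (up to 5 years, two-year follow-up). All of these rest on an assumed entry age of 6, delays of one to three years and assumed placement shares; none is a figure from the article.

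Hypothesis c is ambiguous between plurality and majority and lacks a reference, so meeting it on either reading would not show benefit from implantation. Neither hypothesis delivers the comparison in objective c, and attainment is not what the listed forms record.

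**What to change.** **Hypothesis b.** Take as denominator every enrolled child not yet in school at baseline who reaches the local school-entry age during follow-up. The outcome is in mainstream school at that age, yes or no. Treat children lost before that age as censored.

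**Hypothesis c.** Among school-age children, report the proportion in mainstream school without support with its confidence interval. State whether the comparison is with each other category or with all combined. Testing against 50% is one option, but it supplies no external reference either. Add an adjusted comparison between unilateral, bilateral and bimodal groups, for example adjusting for age and country.

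**Objective c.** Replace attainment with placement.

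**Cost.** These are changes of wording and analysis. Placement and age at implantation are already collected, so no new form appears necessary. Country school-entry ages must be looked up, since no listed form category mentions them, and the reported percentages will probably be less favourable.
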